# Exercise Training in Pregnancy for obese women (ETIP): study protocol for a randomised controlled trial

[name]1,3\*, [name], [name], [name], [name] and [name]

**Background:** Both maternal pre-pregnancy obesity and excessive gestational weight gain are increasing in prevalence and associated with a number of adverse pregnancy outcomes for both mother and child. Observational studies regarding physical activity in pregnancy have found reduced weight gain in active mothers, as well as reduced risk of adverse pregnancy outcomes. There is however a lack of high quality, randomized controlled trials on the effects of regular exercise training in pregnancy, especially those with a pre-pregnancy body mass index (BMI) at or above 30 kg/m^2.

**Methods:** We are conducting a randomised, controlled trial in Norway with two parallel arms; one intervention group and one control group. We will enroll 150 previously sedentary, pregnant women with a pre-pregnancy BMI at or above 30 kg/m^2. The intervention group will meet for organized exercise training three times per week, starting in gestation week 14 (range 12-16). The control group will get standard antenatal care. The main outcome measure will be weight gain from baseline to delivery. Among the secondary outcome measures are changes in exercise capacity, endothelial function, physical activity level, body composition, serum markers of cardiovascular risk, incontinence, lumbopelvic pain and cardiac function from baseline to gestation week 37 (range 36-38). Offspring outcome measures include anthropometric variables at birth, Apgar score, as well as serum markers of inflammation and metabolism in cord blood.

**Discussion:** The results of this trial will provide knowledge about effects of regular exercise training in previously sedentary, obese pregnant women. If the program proves effective in reducing gestational weight gain and adverse pregnancy outcomes, such programs should be considered as part of routine pregnancy care for obese women.

**Trial Registration:** ClinicalTrials.gov: NCT01243554

## Background

In the United States over one-third of reproductive age women are obese (body mass index (BMI)  $\geq 30$  kg/m^2) and another 29% are overweight (BMI 25.0-29.9 kg/m^2) [1]. Maternal obesity is associated with a number of adverse outcomes during and after pregnancy, such as gestational diabetes, preeclampsia, caesarean delivery and children born large for gestational age [2], as well as increased risk for childhood obesity among offspring. In addition, over 60% of overweight women gain more

than recommended during pregnancy [3]. As gestational weight gain is directly associated with maternal weight retained during the postpartum period [3] as well as with offspring adiposity in childhood [4] and in early adulthood [5], excess gestational weight gain could accelerate the obesity epidemic. Current recommendations say that pregnant women should exercise with moderate intensity for 30 minutes or more on most, if not all, days of the week [6]. In general, women are not active enough during pregnancy and women who have a high pre-pregnancy BMI are even less likely to be physically active [7].

Today's knowledge about the importance of exercising regularly in controlling weight gain in pregnancy is

\* Correspondence: [contact]

Department of Public Health and General Practice, Norwegian University of Science and Technology, Trondheim, Norway

Full list of author information is available at the end of the article

mainly based on results from observational studies [4,8-11]. Previous randomized controlled trials of physical activity during pregnancy are few in number and have had varying results. For example, Clapp et al [12] found significantly less weight gain in women who were randomized to high volume of exercise in late pregnancy, compared to moderate or low volumes, whereas others have found no significant effects of exercise training on gestational weight gain [13-15]. The reasons for the divergent results in these randomized trials could be low compliance, high drop out rates and inadequate number of participants in some of the studies, as well as differences in the mode, frequency, intensity and duration of the exercise training. A reduced risk of excessive weight gain has been found in women randomized to lifestyle counselling programs combining diet and exercise [16,17]. In such programs however, it is hard to say if it is the exercise component or other factors that make the women gain less weight in the intervention groups. Thus, there is a lack of good quality randomized controlled trials, assessing short and long term effects of physical activity in pregnancy on mothers and offspring. Especially, there is a need for studies looking at potential effects of regular exercise training during pregnancy in obese mothers.

In this paper, we describe the methods of the Exercise Training in Pregnancy (ETIP) trial, a randomized, controlled trial of physical activity during pregnancy.

## Methods

### Objectives

The primary objective of the ETIP trial is to test the hypothesis that obese pregnant women who exercise in addition to usual pregnancy care will have a lower gestational weight gain compared to women who receive usual care only.

Secondary, the ETIP trial will investigate the effects of exercise training on various pregnancy-related complications, such as insulin resistance, lumbopelvic pain, urinary and fecal incontinence, pelvic floor muscle dysfunction, and prolonged labour. We will also assess possible effects of exercise training on cardiopulmonary parameters as cardiac function, submaximal oxygen uptake, lactate threshold, heart rate recovery, endothelial function, and blood pressure, measured as changes in these parameters from early to late pregnancy. Offspring variables include Apgar score, weight, length and head circumference at delivery, prevalence of large for gestational age (LGA) and small for gestational age (SGA), blood pressure, and body composition, and cord blood markers of inflammation and insulin resistance.

Our hypothesis is that regular exercise training in pregnancy will reduce gestational weight gain and pregnancy-related complications. We also hypothesise that

exercise will increase physical capacity, heart rate recovery and endothelial function, and reduce blood pressure, compared to the control group. Regarding offspring variables, we hypothesise that exercise training will reduce the prevalence of LGA, blood pressure, cord blood markers of inflammation and insulin resistance, as well as improve body composition, and Apgar score.

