The maternal secondary outcome measurements are outlined in Figure 2 and described more in detail below. Blood sampling for fasting glucose concentrations and the other blood markers will be taken after a 10 hour overnight fast, and glucose tolerance will be measured by a 2 hour 75 mg per-oral glucose tolerance test. Gestational diabetes is diagnosed as fasting glucose  $\geq 6.9$  mmol/L or 2 h concentration  $\geq 7.8$  mmol/L [22]. Insulin resistance will be calculated using the homeostasis model assessment (HOMA-IR). We will analyse fasting blood for concentrations of lipids, ferritin, haemoglobin, high-sensitive C-reactive protein, and insulin c-peptide. We will also collect whole blood and serum to be frozen at -80C and stored in a biobank for

[figure not shown]

later analyses of hormones associated with female reproduction and blood markers associated with adiposity and insulin resistance. We will also collect Tempus blood RNA tubes and urinary samples to be frozen for later analyses.

Body height will be measured by a wall mounted height scale. Body composition will be assessed by skinfold thickness during pregnancy and also by dual energy x-ray absorptiometry (DEXA-scan) at three months postpartum. Skinfold thickness will be measured at the right side of the body at the following sites: triceps, biceps, and subscapular, by Harpenden Caliper (Holtain Ltd, UK). Sum of skinfold thickness are measured and used for later calculation of body fat percentage. Waist circumference is measured at all time points at the level of the umbilicus. DEXA (Hologic Discovery-A: Integrity Medical Systems) will be used to measure body composition after 10 hours of fasting, to decrease large variations in hydration status (postpartum only).

Lumbopelvic pain (Disability Rating Index) and physical examination of lumbar spine and pelvic region are done by experienced physical therapists. Tests used are active straight leg raising [23] and the posterior pelvic pain provocation test [24].

Prevalence and severity of urinary- and fecal incontinence will be assessed by questionnaires [25,26], muscle strength measurements, 2D and 3D ultrasound investigation of the pelvic muscles, and clinical examination and palpation of the pelvic floor muscles. Pelvic floor muscle strength, and vaginal squeeze pressure, will be measured using a vaginal balloon catheter with a balloon size of 6.7 × 1.7 cm connected to a pressure transducer [27].

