#### Sample size

Based on prior studies [37,38], the power calculation has taken into account a 6 kg expected and clinically relevant difference between mean weight increases in the control group compared to the training group (between baseline and delivery). Based on this assumption, an independent samples t-test, 5% level of significance and test strength of 0.90, gives a study population of 59 in each group. A 15% estimated drop-out requires a total of 150 included obese pregnant women, 75 enrolled in each arm.

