#### Blinding

Baseline measurements, except for the armband registration of physical activity, will be done before randomisation. Later assessments will be done both blinded (echocardiography, pelvic floor assessments, blood analyses, all offspring variables) and non-blinded to group allocation (weight, skinfold measurements, lumbopelvic pain, oxygen uptake and endothelial function recordings). Although endothelial function recordings are

done non-blinded, the analyses of these data will be done blinded to both group allocation and time of measurement.

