#### Statistical methods

The principal analysis will be done on an intention-to-treat basis; outcome measures will be analyzed according to the treatment arm to which patients are randomized regardless of subsequent crossover or non-adherence. To model the outcome variables over time, we will use a linear mixed effects model [39]. Age, parity, and BMI will be considered as potential covariates to improve precision. We will also do post-hoc comparisons of time points within groups, looking at within-group changes in outcome variables from gestational week 14 to 37, as well as from gestational week 37 to 12 weeks post partum.

In addition to the primary analysis, we will split the women according to if they have actually been exercising during pregnancy or not. The cut-off for this analysis will be: 1) attending  $\geq 42$  organised exercise sessions, or 2) attending  $\geq 28$  exercise sessions + performing  $\geq 28$  home exercise sessions, or 3) performing  $\geq 60$  home exercise sessions. To count as a home exercise session, the exercise should be  $\geq 50$  minutes (either aerobic or strength training) of at least moderate intensity. We also intend to compare women fulfilling the general recommendations for healthy adults of exercising moderately for 30 minutes daily [40], with the ones below this threshold. Results will be given as mean values with 95% confidence intervals. P-values  $< 0.05$  will be considered significant.

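### Secondary outcomes are expressed as change from early to late pregnancy, and each outcome's own baseline value is not among the covariates named for precision; in its ordinary form the mixed model would then compare change scores and lose avoidable precision

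*Protocol*

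**What the plan says.** Protocol, Objectives: the effects on cardiac function, submaximal oxygen uptake, lactate threshold, heart rate recovery, endothelial function and blood pressure are to be "measured as changes in these parameters from early to late pregnancy". The abstract extends the change wording to exercise capacity, physical activity, body composition, serum markers, incontinence and lumbopelvic pain, ending with "cardiac function from baseline to gestation week 37 (range 36-38").

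Protocol, Statistical methods: "To model the outcome variables over time, we will use a linear mixed effects model". The fixed effects are not listed. On precision the section says "Age, parity, and BMI will be considered as potential covariates to improve precision". The outcome's own baseline value is not mentioned.

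Protocol, Blinding: "Baseline measurements, except for the armband registration of physical activity, will be done before randomisation". Apart from the armband, the baseline values are therefore unaffected by allocation and can safely be used for adjustment.

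Two details limit the scope. Under Secondary outcome measures, echocardiography is scheduled at weeks 14, 20 and 32, 48 hours after delivery and three months post partum, so its last visit in pregnancy is week 32, not week 37. Body composition is also assessed by "dual energy x-ray absorptiometry (DEXA-scan) at three months postpartum" only, so that measure has no baseline scan.

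**The concern.** In a randomised comparison of a continuous outcome measured before and after treatment, a difference in change scores subtracts the whole baseline value. Unless the regression of follow-up on baseline has slope 1, this subtracts too much. The excess adds noise and carries part of any chance baseline difference into the estimate.

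The Objectives set directional hypotheses on these outcomes (for example better endothelial function and lower blood pressure), while the Sample size section powers only weight gain. With 59 to 75 women per arm and many secondary outcomes, avoidable variance matters, and modest chance imbalances on some outcomes are to be expected.

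The section does address precision and names three covariates for it. It omits the one that is usually most predictive and is already collected. The named covariates are no substitute: entered as main effects in a model with complete visits, they cancel from the within-woman contrast and leave the arm-by-time estimate unchanged.

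**Working it through.** **Inputs**
- Women per arm: 59 with data, from Sample size. That figure is for the primary outcome, and the SD behind it is not given. An assumed SD of 10 kg reproduces it: 2 × (1.960 + 1.282)² × (10/6)² = 58.4, rounded up to 59. The protocol gives no precision figure for the secondary outcomes.
- Two-sided 5% test (sidedness is not stated; assumed).
- Correlation r between baseline and late-pregnancy value: not given. Assumed range 0.3 to 0.7, with 0.8 and 0.9 as a check.
- Equal SD s at both visits: assumed.

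**Step 1. What the ordinary mixed model estimates.** With arm, time and arm-by-time, each of the four arm-by-visit means is free. With both visits complete, the interaction is (late minus baseline mean in the exercise arm) minus (the same in the control arm), which is the difference in change scores. In simulated trials with 59 per arm the two agreed to 2 × 10⁻¹⁵. If some women have only a baseline visit, the equality is approximate.

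**Step 2. Variances per woman.**
- Change score: 2(1 − r)s²
- Baseline-adjusted: (1 − r²)s²
- Ratio, adjusted to change: (1 + r)/2

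The direction does not depend on equal SDs. With SDs s₀ and s₁, change variance minus adjusted variance is s₀² + s₁² − 2r s₀s₁ − s₁²(1 − r²) = (s₀ − r s₁)², which is never negative. The cost of estimating the slope is negligible at this sample size.

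**Step 3. Size of the loss.** The standard-error loss is 1 − √[(1+r)/2]. The extra women that a change-score analysis needs for equal precision is 2/(1+r) − 1.

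| r (assumed) | Variance ratio | Variance lost | Standard error lost | Extra women |
|---|---|---|---|---|
| 0.3 | 0.65 | 35% | 19% | 54% |
| 0.5 | 0.75 | 25% | 13% | 33% |
| 0.7 | 0.85 | 15% | 8% | 18% |
| 0.8 | 0.90 | 10% | 5% | 11% |
| 0.9 | 0.95 | 5% | 2.5% | 5% |

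**Step 4. Illustrative power.** For an assumed effect of 0.5 SD of a single measurement, 59 per arm, change score against baseline-adjusted:
- r = 0.3: 62% against 81%
- r = 0.5: 77% against 87%
- r = 0.7: 94% against 96%

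**Step 5. Chance imbalance.** The change-score estimate minus the adjusted estimate is −(1 − r) times the baseline difference between arms. A 0.2 SD imbalance therefore shifts the change-score result by 0.14, 0.10 or 0.06 SD at r = 0.3, 0.5 or 0.7, in the direction opposite to the imbalance. The standard error of a baseline difference with 59 per arm is √(2/59) = 0.184 SD, so 0.2 SD is 1.09 standard errors. An imbalance at least that large, in either direction, is expected for about 28% of outcomes.

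**Step 6. The other parametrisation.** Simulation with 59 per arm and 300 runs, variances scaled so that theory gives 2(1 − r) and 1 − r²:

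| r | Change score | Unconstrained mixed model | Baseline as covariate | Equal baseline means |
|---|---|---|---|---|
| 0.3 | 1.335 | 1.335 | 0.916 | 0.918 |
| 0.5 | 0.997 | 0.997 | 0.869 | 0.844 |
| 0.7 | 0.598 | 0.598 | 0.482 | 0.479 |

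Each variance has a simulation error of about √(2/300) = 8%, so the pattern matters more than the exact ratios. The unconstrained model carries the full change-score loss, and the model with equal baseline means recovers it.

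**The case against.** The strongest reply is that the protocol fixes no inefficient analysis. The change wording is in the abstract and Objectives, which say what is measured. Statistical methods plans a mixed model over time, in which baseline can be the first repeated outcome, and does not say whether the arms share a baseline mean. If they do, nothing is lost. Change wording does not rule out adjustment either: regressing change on arm and baseline gives the same arm effect as regressing the late value on arm and baseline. The covariate list is tentative and not closed, and such detail often sits in a statistical analysis plan.

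Most of this stands. A reader might infer that the protocol rejects baseline adjustment and so forfeits 15% to 35% of its precision. The text does not support that: the parametrisation is open, and the range rests on an assumed r of 0.3 to 0.7, is a variance figure, and shrinks for highly correlated outcomes. A reader might also infer that change scores bias the result away from zero. They do not. Over repeated randomisation the contrast is unbiased, and in a given trial the shift can go towards or away from zero.

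What the reply does not remove is that the protocol takes up precision, names covariates for it, leaves out the most useful one, and words its effects in the way that leads to the ordinary model. The mixed model alone does not recover the precision.

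**Conclusion.** The point holds conditionally. If the mixed model is fitted with arm, time and arm-by-time, the secondary comparisons are change-score comparisons. They then lose 35%, 25% or 15% in variance at an assumed r of 0.3, 0.5 or 0.7, and 10% to 5% at 0.8 to 0.9, assuming equal variances. If baseline means are constrained equal, or baseline is a covariate, the loss is about zero.

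It applies to continuous maternal secondary outcomes with a value taken before randomisation. It does not reach armband activity (its first recording is exempt from the rule that baseline precedes randomisation), DEXA (no baseline scan), or prolonged labour and pre-eclampsia (no baseline value). It is a matter of efficiency and of chance imbalance within the trial, not of validity.

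**What to change.** Add to Protocol, Statistical methods, that for each continuous outcome measured before randomisation the between-arm effect is adjusted for the woman's own baseline value. Either of two forms will do: constrain baseline means to be equal across arms in the mixed model (omit the arm main effect and keep arm-by-time), or enter baseline as a covariate. Name the visit at which the effect is read: week 37, or week 32 for echocardiography, and the post partum visit where relevant. Exclude outcomes without a pre-randomisation value.

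The Objectives and abstract can keep their wording, and outcomes may still be reported as change. The cost is one or two sentences, with no new data, visits or participants.

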### Participants and setting

We invite pregnant women with self-reported pre-pregnancy BMI  $\geq 30$  kg/m^2 to participate in the trial. Women are eligible if they are 18 years or older, with a singleton live fetus at an 11-14 weeks ultrasound scan. Exclusion criteria are pregnancy complications, high risk for preterm labour or diseases that could interfere with participation, and habitual exercise training (twice or more weekly). The women are given information about the project and will be recruited through the ordinary visits at general practitioners and midwives, and at outpatient clinics at the hospitals. Also, information about the study and invitation to participate is sent along with the invitation to come for routine ultrasound scan in week 18.

The trial will be conducted at the Norwegian University of Science and Technology and the St.Olavs Hospital, Trondheim University Hospital. The recruitment started in September 2010 and will continue until the needed number of participants is included, anticipated until the end of 2012. Participating women get infant food worth \$85 US dollars.

### Randomisation and allocation

After initial assessments, the women will be randomly assigned to either intervention or control (1:1 randomisation, Figure 1). Allocation is performed by a web-based randomisation system developed and administered by another unit at the university to ensure blinding. The randomisation will be in blocks with varying block size.

### Intervention

We invite the training group to participate in an exercise program that we have specially designed for pregnancy, including aerobic activity, specific exercises for stabilization of the lower back and pelvis, and strength exercises for the pelvic floor muscles that we have specially designed for pregnancy. We conduct training groups for a total of 60 minutes four times weekly at the hospital. We ask the women to come to exercise training a minimum of twice weekly between 14 and 37 weeks of gestation. We also encourage the women to come for exercise training even after week 37. The endurance training consists of a 10 minute warm-up followed by walking on treadmills for 25 minutes. The intensity will be moderate, reaching ~80% of their

[figure not shown]

maximal capacity in periods (corresponding to Borg scale 12-15) [18].

In addition, we instruct intervention women in a 50 minute home exercise program which we encourage them to complete at least once per week (35 minutes endurance training and 15 minutes strength exercises). We also teach pelvic floor muscle exercises to do daily. We also recommend the women to be physically active in every-day life. Adherence is strongly emphasized and registered in the women's personal training diary and the reports from the persons leading the training groups. During the training period, the subjects will go through motivational interviewing [19]. This is a client-centred therapeutic method to enhance readiness for change and to elicit the client's own motivations for change. Each woman will go through a 30 minute session of motivational interviewing in each trimester. They will also receive a weight gain curve that shows the recommended weight gain throughout pregnancy,

based on 2009 Institute of Medicine guidelines [20]. The training protocol follows recommendations from the Norwegian Health Directory [21] and the American College of Obstetrics and Gynecology [6]. Specific adjustments are made to the exercise program if needed (for example by using a stationary bike instead of treadmill walking and by modifying the strength exercises to the actual strength level of the participants).

Women in the control group will receive the customary regular consultations with midwife, general practitioner or obstetrician. They are not discouraged from exercising on their own. Neither group will receive special recommendations about diet, beyond what is given through standard antenatal care. In Norway, the pregnancy care is free of charge. Routine prenatal visits are done by general practitioners, midwives, or a combination of the two, and are usually undertaken in gestational weeks 8-12, 24, 28, 32, 36, 38, 40, and 41. In addition, women are invited to an ultrasound scan is

gestational week 18. There is currently no knowledge about the actual advices about physical activity that pre-natal care providers give to pregnant women, but the guidelines from the Norwegian Health Directory [21] are in line with the international guidelines [6].

Study assessment visits

We will see women for research visits at baseline (12-16 weeks of pregnancy), and again in week 37 (range 36-38), as well at three months post partum (Figure 2). We also obtain clinical measures that are collected during the delivery hospitalization as well as through primary care.

Primary outcome measure

The primary outcome measure is gestational weight gain, calculated as the difference between weight measured at the time of inclusion and weight just before delivery. We measure maternal body weight at enrolment and before delivery to the nearest 0.1 kg with a calibrated electronic scale (SECA 770, Medema, Norway) with participants wearing indoor clothing, without

shoes. Hospital staff will measure weight during the delivery hospitalization using a different scale than at baseline. We will calibrate the scales to ensure comparability. If the hospital staff forget to weight the women, we will use their self-reported weight at the time of delivery as the outcome measure.

Secondary outcome measures

The maternal secondary outcome measurements are outlined in Figure 2 and described more in detail below. Blood sampling for fasting glucose concentrations and the other blood markers will be taken after a 10 hour overnight fast, and glucose tolerance will be measured by a 2 hour 75 mg per-oral glucose tolerance test. Gestational diabetes is diagnosed as fasting glucose  $\geq 6.9$  mmol/L or 2 h concentration  $\geq 7.8$  mmol/L [22]. Insulin resistance will be calculated using the homeostasis model assessment (HOMA-IR). We will analyse fasting blood for concentrations of lipids, ferritin, haemoglobin, high-sensitive C-reactive protein, and insulin c-peptide. We will also collect whole blood and serum to be frozen at -80C and stored in a biobank for

[figure not shown]

later analyses of hormones associated with female reproduction and blood markers associated with adiposity and insulin resistance. We will also collect Tempus blood RNA tubes and urinary samples to be frozen for later analyses.

Body height will be measured by a wall mounted height scale. Body composition will be assessed by skinfold thickness during pregnancy and also by dual energy x-ray absorptiometry (DEXA-scan) at three months postpartum. Skinfold thickness will be measured at the right side of the body at the following sites: triceps, biceps, and subscapular, by Harpenden Caliper (Holtain Ltd, UK). Sum of skinfold thickness are measured and used for later calculation of body fat percentage. Waist circumference is measured at all time points at the level of the umbilicus. DEXA (Hologic Discovery-A: Integrity Medical Systems) will be used to measure body composition after 10 hours of fasting, to decrease large variations in hydration status (postpartum only).

Lumbopelvic pain (Disability Rating Index) and physical examination of lumbar spine and pelvic region are done by experienced physical therapists. Tests used are active straight leg raising [23] and the posterior pelvic pain provocation test [24].

Prevalence and severity of urinary- and fecal incontinence will be assessed by questionnaires [25,26], muscle strength measurements, 2D and 3D ultrasound investigation of the pelvic muscles, and clinical examination and palpation of the pelvic floor muscles. Pelvic floor muscle strength, and vaginal squeeze pressure, will be measured using a vaginal balloon catheter with a balloon size of 6.7 × 1.7 cm connected to a pressure transducer [27].

Psychological well-being and postnatal depression will be assessed using standardized questionnaires (The Psychological General Well-Being inventory [28] and The Edinburgh Postnatal Depression Scale [29], respectively). Also, the women will fill in a questionnaire about delivery expectancy (The Wijma Delivery Expectancy/Experience Questionnaire [30]) Quality of life will be assessed by the generic SF-8 Quality of life questionnaire [31]. To register diet during the intervention period, the women will fill in a validated Norwegian quantitative food frequency questionnaire [32].

Prevalence of pre-eclampsia will be registered by use of the women's health certificates. We will measure systolic and diastolic blood pressure with an automatic device, after 15 minutes of supine resting and use the average of three repeated measurements taken with two minutes intervals. We will measure endothelial function by flow-mediated dilatation of the brachial artery using ultrasound (Vivid 7, GE Vingmed Ultrasound, Norway). The women will fast and abstain from exercise, caffeine, and smoking for ten hours, and rest for 10 minutes

before the measurements. The recordings are done 5 cm above the antecubital fossa before inflation of a pneumatic cuff on the lower arm for 250 mm Hg for five minutes, and again directly after cuff release and for five minutes. The responses will be analysed by a automatic detection program, and will be reported both as absolute changes and as responses normalized by dividing the percentage change in diameter by the shear rate.

Physical activity will be registered by questionnaires. Both groups will also wear a activity monitor (Sensewear Armband, APC Cardiovascular, UK) to register their level of daily physical activity for one week in early (before week 17), mid (week 19-24) and late (after week 28) pregnancy. This armband includes a two-axis accelerometer, a heat flux sensor, a galvanic skin response sensor, a skin temperature sensor and a near-body ambient temperature sensor, and has been validated during pregnancy (Berntsen et al, In review/in press *Acta Obstetrica et Gynecologica Scandinavica*). In addition, the training group will fill in a training diary.

Maternal cardiac function will be measured using echocardiography. The assessments will be done at week 14, week 20, and week 32, as well as 48 hours after delivery, and again at three months post partum (Figure 2). A full resting echocardiogram will be performed with a Vivid 7 scanner (GE Vingmed Ultrasound, Horten, Norway) using a phased-array transducer. Three cine loops from the three standard LV apical planes (four-chamber, two-chamber and long-axis), right ventricle and LV parasternal view will be recorded in B- mode and tissue Doppler mode simultaneously. Conventional Doppler flow parameters will be measured as well as tissue Doppler imaging with pulsed tissue Doppler in the AV-plane and strain/strain rate of the 16 segments of the left ventricle (with tissue Doppler and speckle tracking). For automated identification of myocardial segments and analysis, we will use a customized post-processing system (GcMat, GE-Vingmed, Horten, Norway).

Multistage submaximal exercise tests will be done on treadmills. After familiarizing with walking on a treadmill and 2-3 minutes of warming up, the test begins with walking at 4,5 km/h and 0% inclination. Each stage is 4 minutes and the inclination is elevated 3% each stage. Heart rate and oxygen uptake will be measured continuously during the test. Blood lactate, blood pressure and perceived exertion (according to the Borg 6-20 scale, [18]) will be recorded at the end of each stage. Tests are terminated if the subjects are feeling unwell (have symptoms of pain, nausea, or dizziness), if the heart rate exceeds 185 beats per minute, or if systolic and diastolic blood pressure exceeds 200 and 100 mmHg, respectively.

At delivery, we register mode of delivery and potential complications. Offspring variables include are outlined in Figure 2, and include the child's condition at birth and in the newborn period, birth weight, birth length, head circumference, subscapular and triceps skinfold thickness, upper-arm- and mid-abdominal circumferences, cord blood markers of inflammation and insulin resistance, and blood pressure. The child's condition include Apgar scores at one and five minutes as recorded by the attending mid-wife or physician, birth traumas, need for extra oxygen, transfer to neonatal intensive care unit, and diagnosis. The anthropometric measurements will be standardized according to Vik et al [33].

We intend to follow the children at age 3 and 12 months. At these time points we will also register breast feeding and the use of supplementary feeding, as well as crying behaviour according to Wessel et al [34]. Neuro-motor development will be recorded through milestones, and by using the age and stages questionnaire at 12 months of age [35]. This instrument has been validated in Norway [36]. We also intend to follow these children for a longer time in order to study possible long term effects of in utero exposure to maternal exercise training.

